### Survey Completion (Months 0, 3, 6, and 12)

REDCap is being used to monitor and manage all survey data collected as part of this study. Surveys will be conducted at baseline (month 0 [M0]), month 3 (M3), month 6 (M6), and month 12 (M12) and used to collect data on condom use attitude, behavioral capability, self-efficacy, and intention, along with details of any partnered sexual activity and condom use that has occurred in the previous 3-month period. The surveys will also be used to measure the experience of partner resistance to condom use and to collect health economic data. There are between 63 and 76 core items per survey (depending on time point), with data largely being collected using fixed response items and Likert scales (see Multimedia Appendix 5 for survey items). The baseline survey will additionally collect participant’s contact details to enable communication with participants regarding the completion of follow-up surveys, and basic demographic data. The M3 survey will also be used to collect self-reported data on participant engagement with the intervention.

Completion of the baseline survey is scheduled immediately after consent is provided. All other survey completion will be triggered by email. Participants who do not complete the survey will be sent up to 3 reminders (delivered by SMS text message). Subsequently, if no response is received, 1 email and 1 telephone call will be made to prompt completion. During the telephone call, participants will be given the option to verbally respond to a reduced set of survey questions. Finally, if there is still no response, a paper-based version of the survey will be posted out with a stamped addressed return envelope. Those who have not provided any data 20 days after the initial survey is sent out will be classed as nonresponder. Surveys will continue to be sent to nonresponders (as well as chlamydia tests––see below) at subsequent time points unless a participant asks to be withdrawn from the study.

### Chlamydia Testing (M0, M3, and M12)

Chlamydia tests will be processed by freetest.me at M0, M3, and M12. The chlamydia test at M0 is triggered by participants when they order a self-sampling kit through the freetest.me website immediately before receiving the study invite (see “recruitment” above). Participants will be asked to self-report their result, and any treatment received if applicable, through SMS text message. A single SMS text message reminder will be sent to participants who do not respond. Those who have not provided this data 4 weeks after the SMS text message contact is made will be classed as nonresponders.

The chlamydia tests at M3 and M12 will be processed differently to that at M0. For this purpose, chlamydia self-sampling kits will be sent directly from the study team to participants. One week before posting the kits, participants will be sent an SMS text message asking them to confirm or amend their postal address. The kits that participants receive at M3 and M12 will contain the usual user instructions to collect the sample and return by Freepost to freetest.me for processing. Participants will be sent 3 SMS text message reminders to complete the test kit. If the test kit still has not been returned after this point, 1 phone call will be made to prompt return. Those who have not returned their kit 30 days after it is posted out will be classed as a nonresponder. Participants who have a positive test result at M0, M3, or M12 will receive 1 item within SMS text message survey 2 weeks post results to record whether their infection has been treated or not. If treatment is incomplete, or the participant does not respond, they will be sent 1 reminder SMS text message to obtain this information. Each local NHS trust will be informed of any positive cases (for participants residing in their local authority area) so that they can provide appropriate treatment and follow-up.

### Randomization

Randomization of participants to trial groups in a ratio of 1:1, is fully automated, and fully concealed within REDCap software, and will take place following completion of the M0 survey. Before randomization of each participant, the research team will manually check that each individual is unique, by cross-checking their identifying information (name, email address, postal address, mobile phone number, and freetest.me order number) with participants already within the sample. They will also check that the participant has answered the baseline survey with reasonable care (ie, no evidence of random responding or completion under the expected minimum time). Those not meeting these criteria will not be randomized. Participants will be blind to group allocation and the research team will be unable to influence any aspect of this procedure. The randomization list will be generated by the study statistician who will monitor randomization on a weekly basis during active recruitment to ensure that the algorithm is being correctly applied. Randomization will be at the individual level as control group contamination is not anticipated (although this will be monitored to determine the suitability of this approach for the definitive trial). Stratification across groups, using randomly permuted blocks (ethnicity, sexual identity, deprivation) will be performed to balance participants across the trial arms.

### Intervention Access, Content, and Tracking

Participants will be individually randomized within the stratifications into 1 of 2 groups: usual care or Wrapped plus usual care (see “Wrapped website” and “comparator website” below for further details on the respective interventions). Participants will be directed to their allocated intervention following randomization through a hyperlink. All participants will be free to interact as much or as little with the respective materials; participants will be emailed the hyperlink to enable repeat visits. An email reminder to visit the intervention will be sent to all participants who have not done so 2 weeks after first access is provided.

#### Wrapped Website

See Multimedia Appendix 6 for the intervention logic model which presents the theoretical model and an outline of intervention components. Newby et al [14] have provided a detailed description of intervention content reported in line with Template for Intervention Description and Replication guidance and have provided screenshots, images of intervention materials, and example videos.

#### Comparator Website

Usual care is the comparator. Existing STI self-sampling websites typically provide only basic information on STIs and condom use to their users [21]. To replicate this level of health promotion, and to provide an equivalent “intervention” experience for those in the control group, a stand-alone WordPress website presenting comparable basic information has been created [22]. The same basic information is also provided on the Wrapped website.

#### Analytics Data

Participant access to and engagement with their allocated website will be tracked. There is no minimum acceptable level of engagement––all participants will be allowed to continue in the trial regardless of their level of interaction with the material. Tracking will occur in the background (with each participant’s explicit consent) to ensure that it is unobtrusive. Data will be collected within the Wrapped website itself using an analytics package called Matomo, a secure open-source platform [23] (see Multimedia Appendix 7 for details on what will be measured). Analytics data will be used to calculate intervention dose received and to identify any fixable “friction points” in the user journey that may adversely affect usability.

### Primary Outcome Measures

Primary outcome measures are as follows:

The percentage of freetest.me users recruited to the feasibility RCT.This will be assessed as the number of participants randomized out of those using freetest.me in the 4 local authority areas, that is, all those exposed to the recruitment advert.The percentage of randomized participants with a valid primary outcome measure. This will be assessed as the percentage of randomized participants who provide a chlamydia test result at M12.

### Secondary Outcome Measures

Secondary outcome measures are as follows:

Percentage of randomized participants with outcome data required to measure cumulative incidence of chlamydia (measured using M3 and M12 chlamydia self-sample, and the relevant item within M3, M6 and M12 surveys).The distribution of Index of Multiple Deprivation quintile among users of freetest.me over the 3-month recruitment period, compared to that of the final sample, within each of the 4 recruitment areas.The number of randomized participants with a valid primary outcome measure at M12 by group (gender, ethnicity, sexual identity, deprivation, randomized groups, and chlamydia diagnosis at baseline).The number of randomized participants testing positive for chlamydia at M12 in the intervention and the control group.Attrition curves comparing the percentage of valid participants in the trial at randomization, M3, M6, and M12 plotted for the intervention and control arms (dropout attrition).Completeness of data from outcome measures that would be needed in a definitive trial (ie, self-report of chlamydia result at baseline, results from biological samples, demographic information, self-report of condom use and chlamydia infection, and data needed for cost-effectiveness and cost-utility analyses).The percentage of freetest.me users randomized following each of the different recruitment messages employed.The percentage of valid participants in the 2 arms that do not achieve predetermined intervention “goals” (ie, do not follow instructions within each component of the Wrapped website to their culmination, for example, ordering a sample pack, or watching a suggested video), and the bounce rate for home and content pages.Completeness of data on costs and resource use that would be needed for the economic evaluation in the definitive RCT.Proportion of participants in the control group who report (at M12) any exposure to Wrapped.The total number of adverse events reported during the course of the study (inadvertent disclosure that sexually active or testing for STI if overseen using Wrapped, initiation or change in the consumption of pornography, or other).

### Sample Size

At least 60 participants per arm are recommended to allow proportions to be estimated with good precision [24]. This is inflated to allow for an estimated 25% nonreturn of initial chlamydia self-test sample (based on freetest.me statistics; 60/0.75=80) and a further estimated 30% dropout over the course of the feasibility trial (a conservative estimate based on 19% dropout achieved in Free et al [25] sexual health feasibility RCT (80/0.7=114 per arm). Based on this, the total sample size required for the present fRCT has been calculated as 230 participants.

### Progression Criteria

The following criteria will be used to inform progression to a full trial:

The proportion of freetest.me users recruited to the feasibility trial is sufficient to obtain the sample size required for the definitive RCT (sample size for the definitive RCT will be determined using data from multiple sources, including chlamydia positivity in the control group of the present fRCT and national level data on chlamydia positivity among young people testing for STIs through the internet (used to estimate the level of chlamydia positivity in the target population), expert opinion on what would be a clinically meaningful reduction in chlamydia positivity for the target population, typical effect sizes achieved in comparable studies, and the size of the available sampling pool for the future RCT).A total of 60% (138/230) of participants (those randomized) followed up for the definitive RCT primary outcome measure at M12Index of Multiple Deprivation quintile distribution for the final sample is comparable to that of individuals in the sampling pool (freetest.me users in the partner local authority areas).Adverse events are judged as sufficiently infrequent and/or serious to cause concern.

The progression decision will be determined by the independent Study Steering Committee (SSC), in conjunction with the Data Monitoring and Ethics Committee, based on achievement of all the above criteria, or convincing evidence that any 1 criterion is amenable for necessary improvement.

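### The fourth progression criterion is met, as printed, by adverse events serious enough to cause concern, and no other section corrects it

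*Protocol article*

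**What the plan says.** The Progression Criteria section of the protocol article introduces its list with "The following criteria will be used to inform progression to a full trial". Four items follow: enough recruitment for the definitive trial, 60% (138/230) followed up at month 12, a comparable deprivation distribution, and "Adverse events are judged as sufficiently infrequent and/or serious to cause concern".

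The section then says who decides: "The progression decision will be determined by the independent Study Steering Committee (SSC), in conjunction with the Data Monitoring and Ethics Committee". The decision is to be "based on achievement of all the above criteria, or convincing evidence that any 1 criterion is amenable for necessary improvement".

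Elsewhere, Secondary Outcome Measures defines the adverse-event outcome as "The total number of adverse events reported during the course of the study", with the event types named but no threshold or grading of seriousness. Risks, Support, and Safeguarding describes how the research team discusses each disclosed event and seeks advice where required. Monitoring sets up the two oversight committees. Strengths and Limitations refers to the progression criteria being met only in general terms.

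**The concern.** The decision rests on the criteria being achieved, so each item must describe a state that favours going ahead. The first three do. The fourth attaches the idea of causing concern to the word for serious, so that worrying seriousness becomes something to be achieved. The frequency limb, read with the same ending, says that events are rare enough to cause concern, which has no sensible meaning.

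Progression criteria are written in advance so that the decision can later be checked against them. A reader who compares the committees' decision with this sentence cannot do so without first rewriting it. The item concerns harm in people aged 16-24 years, where the event types named in the article include inadvertent disclosure of sexual activity or STI testing.

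The closing clause raises a lesser question. It does not say that the improvable criterion is one that was missed, how many may be missed, or what is required of the others.

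**Working it through.** **Figures.** The point disputes no number. From the Sample Size section: 60/0.75 = 80; 80/0.70 = 114.3, rounded up to 115 per arm; 2 × 115 = 230. The article prints 114 per arm, which is the unrounded-up value (2 × 114 = 228); the stated total of 230 is reproduced by rounding up. The follow-up criterion is 138/230 = 0.60. None of this changes.

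**Fourth criterion.** Inputs: the printed sentence, and the statement in the same section that the criteria are to be achieved. Read the frequency limb generously, as *infrequent enough*. Let the seriousness limb mean what it says, *serious enough to cause concern*. The connective allows *or* and *and*. The last column is the ordinary safety condition: met only when events are neither too frequent nor too serious.

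| Events are | Printed, *or* | Printed, *and* | Safety condition |
|---|---|---|---|
| frequent, not serious | not met | not met | not met |
| frequent, serious | met | not met | not met |
| infrequent, not serious | met | not met | met |
| infrequent, serious | met | met | not met |

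- Under *or*, the printed text differs from the safety condition in rows 2 and 4: serious events pass whatever their frequency.
- Under *and*, it differs in rows 3 and 4: the benign case fails, and only rare but concerning events pass.
- Row 4 is wrong under both readings.

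**Search for a correction.** Of the sections that touch on adverse events or on the criteria, Secondary Outcome Measures gives a count, Risks, Support, and Safeguarding gives a handling procedure for individual events, Monitoring gives the committees, and Strengths and Limitations gives no content for the criteria. None states how adverse events bear on progression, so none repairs the sentence.

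**Closing clause.** Let each of the four criteria be met, unmet but improvable, or unmet and not improvable: 3^4 = 81 combinations. Two sensible readings differ:

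- At most one criterion may be unmet, and it must be improvable: 1 + 4 = 5 combinations allow progression.
- Any number may be unmet, provided each is improvable: 2^4 = 16 combinations allow progression.

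These are counts of combinations, not probabilities. They show only that the number of criteria that may be unmet affects the rule and is not stated.

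**The case against.** The best reply is that this is a slip that nobody would act on. Half of the sentence points the right way, the other half is visibly broken, and an experienced committee would supply the missing negation. The criteria inform a judgement by two oversight committees and do not operate mechanically. Nothing in the outcomes, sample size, analysis or participant procedures depends on the sentence. All of this stands, and it limits the consequence. It does not make the sentence correct, and nothing else in the article states the intended rule.

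Two stronger readings are tempting and should not be drawn.

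- A reader might infer that this sentence is the only safeguard between the feasibility trial and a full trial. It is the only listed criterion on adverse events, but the Data Monitoring and Ethics Committee shares in the decision, and disclosed events are reviewed during the trial under Risks, Support, and Safeguarding.
- A reader might infer from the closing clause that one improvable criterion overrides the failure of the others. Taken with complete literalness, the clause would allow 81 − 16 + 1 = 66 of the 81 combinations. But the words "or convincing evidence that any 1 criterion is amenable for necessary improvement" read most naturally as an exception for a criterion that fell short: they call for convincing evidence, and for improvement that is necessary, which points to a missed criterion. The article does not say that the others may fail.

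**Conclusion.** The fourth progression criterion is wrong as written. Its seriousness limb is reversed, its frequency limb does not parse, and no other section corrects it. On the table above, each reading of the connective gives the wrong result in two of four cases, and both wrongly accept rare but concerning events. This rests on the printed sentence and on the section's own statement that the criteria are to be achieved. That a negation was lost in drafting is an inference, though a likely one.

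The size is that of a wording error in a decision rule. It needs correcting because the rule must be auditable, not because there is any sign that the committees would follow it literally. The closing clause is not an error of the same kind; it is incomplete and merits a clarification only.

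**What to change.** Restate the fourth criterion so that achieving it means no concern, for example: *Adverse events are judged neither so frequent nor so serious as to cause concern.* What counts as concerning stays with the oversight committees; no threshold is proposed here.

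As a secondary clarification, have the closing clause say three things: that the criterion judged improvable is one that was not achieved, how many criteria may be unmet, and that the remaining criteria must be achieved. The number is for the trial team to agree with the two committees.

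The cost is two sentences and the committees' agreement. No redesign, new data or recalculation is needed. Because the article reports data collection as complete in December 2022, the correction should be dated and should say whether it was agreed before the committees considered the adverse-event results.

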### Ethical Considerations

Ethical approval was obtained from the NHS East Midlands—Leicester Central Research Ethics Committee (reference 20/EM/0275) and the trial was registered with the ISRCTN (ISRCTN17478654). To participate, all individuals will be required to provide informed consent. All participants will receive a £65 (US $79.95) payment in the form of vouchers to recompense for time spent completing the research activities. All research data will be deidentified before analysis and reporting.

### Data Management and Analysis

#### Data Management

All trial data will be collected in REDCap, a secure data management program hosted on a university server. REDCap will create a unique ID for each participant at the point of consent. All activity will be associated with this unique ID, enabling data across time points to be easily and accurately linked. Analytics data will be stored within Matomo and the Wrapped website, also linked to the unique ID. Only the research team will have access to data stored on REDCap, Matomo, and the Wrapped website. At the end of data collection, all data captured through these platforms will be exported to a password-protected folder for analysis purposes. Only the research team will have access to this folder. Consent data will be separated from all other data (research data) through storage in 2 separate folders. For the research data, at the point of export, all identifying data will be removed and the remaining data linked using the unique participant ID before cleaning. Once the research team agrees that all data is present and complete, all data present in REDCap, Matomo, and the Wrapped website will be permanently deleted. Research data will remain in the password-protected folder until analysis is complete after which it will be deleted. Consent data will be kept for 6 years before deletion. In line with the funder’s requirements, a copy of the raw anonymized research data will be deposited within the University of Hertfordshire Research Archive (UHRA [26]) and made available indefinitely on an open-access basis.

#### Statistical Analysis

Researchers performing the analysis (KN, KB, LJ, and SB) will be blinded to participant allocation. Quantitative data will be analyzed descriptively. Measures of location and dispersion, including means and SDs, medians and IQRs, and number and percent for categorical variables, will be used to describe the data at baseline and at each follow-up time point. CIs will be calculated and presented as appropriate. All analyses will be performed using SPSS (version 28; IBM Corp). As with the raw data, the syntaxes used for analysis and the output generated will also be deposited within the UHRA and made available indefinitely on an open-access basis.

### Nested Qualitative Study

A nested qualitative study will be conducted during the fRCT. The aims of this study will be to explore participant’s views and experiences of the Wrapped intervention, experience of trial procedures and materials, and perceptions of whether and how the intervention has changed their condom use beliefs or behavior.

Approximately 30 individuals (number to be determined by data saturation) participating in the fRCT will be invited to take part. All participants will receive a £20 (US $24.6) voucher in recognition of their time. Participants will be asked at baseline (single question in survey) whether they are willing to take part in a semistructured telephone or video call interview and if so, to provide suitable contact details.

Participants will be purposively selected to create a varied sample representing different demographic criteria, completers and noncompleters from both trial arms, those with varying levels of intervention engagement, and those thought to have experienced specific events that could influence dropout. Selected individuals will be contacted and directed to a new project page on REDCap where they will be asked to provide informed consent to take part in this additional aspect of the study.

Interviews will last up to 1 hour and will be fully transcribed before analysis. Framework analysis [27] will be used to analyze the data.

At the end of each interview, a second aspect of the qualitative study will be discussed with the participants. This is interviewing sexual partners to better understand any changes in condom use decision-making in light of the intervention. After the interview, an email invitation will be sent to the participant which they can choose to forward to their partner if they wish. It will then be up to the sexual partner to contact the research team if they want to participate. They will be given the option to email or telephone the research team if they have any questions, or simply to follow a hyperlink straight to the relevant project page on REDCap. Here, they will be required to provide informed consent to take part in the study. All data will be collected, processed, and analyzed as described above for primary interviewees. Each individual who participates will be given a £20 (US $24.6) voucher in recognition of their time.

